**Harrel’s concordance index**

Harrel’s concordance I=index (C-Index) is a goodness of fit measure where the number of concordant pairs is divided by the number of comparable pairs. Comparable pairs are any pair of participants from the sample, that is, the number of comparable pairs is
*n*×(
*n*–1)/2. Among all comparable pairs, concordant pairs are the cases where the participant with higher rank (severe anemia=1, moderate anemia=2, mild anemia=3, healthy=4, above normal=5) using SpHb measurements is also the participant with higher rank using CBC measurements. Bootstrap confidence intervals can be similarly obtained for weighted Kappa and Harrel’s C-Index where repeated measures from the same participant will be selected or not selected together.

$$c=\frac{no.of\;concordant\;pairs}{no.of\;concordant\;pairs+no.of\;discordant\;pairs}$$

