### Aim and objectives

The primary aim of this study is to evaluate whether total hemoglobin measures using the Masimo SpHb continuous non-invasive monitoring device are accurate as compared to gold standard CBC laboratory tests using peripheral venous blood samples. To achieve this aim, three statistical objectives were identified:

1.To estimate the level of deviation and agreement between SpHb and CBC values longitudinally.2.To calculate the level of agreement between SpHb and CBC values among binary (healthy versus anemic) and ordinal (mild, moderate, severe anemia versus normal) measures longitudinally.3.To describe sociodemographic and clinical factors affecting the difference between SpHb and CBC values.

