**Weighted Cohen’s kappa**

Weighted Cohen’s kappa is a measure of interrater reliability for ordinal or categorical items, in this case, for anemia severity (mild, moderate, severe, healthy, above normal). Linear or quadratic weights are assigned to different combinations of SpHb category (i) + CBC category (j). The equation for weighted κ is below, where i, j represents the category judging from SpHb and CBC respectively. Furthermore, w
_ij_, O
_ij_ and e
_ij_ are elements in the weight, observed counts, and expected counts matrices, respectively. 

$$\kappa =1-\frac{\sum \;}{}\frac{\sum_{i=1}^{4}\;\;\sum_{j=1}^{4}\;w_{ij}o_{ij}}{\sum_{i=1}^{4}\;\;\sum_{j=1}^{4}\;w_{ij}e_{ij}}$$

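### The two ordinal agreement statistics contradict their own definitions: the C-index has two different denominators, and weighted kappa sums four categories where five are listed

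*Protocol article*

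**What the plan says.** All references are to the protocol article.

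- **Harrel's concordance index, text.** The index is described as one "where the number of concordant pairs is divided by the number of comparable pairs". The next sentence states "Comparable pairs are any pair of participants from the sample" and gives the count as n(n-1)/2. A concordant pair is one in which the participant ranked higher on SpHb is also ranked higher on CBC, so a pair tied on either method is not concordant.
- **Harrel's concordance index, formula.** The denominator is concordant plus discordant pairs. Discordant is not defined, and no rule for ties is given.
- **Rank scale for the C-index.** Five ranks: "severe anemia=1, moderate anemia=2, mild anemia=3, healthy=4, above normal=5".
- **Weighted Cohen's kappa, text.** Five categories: "for anemia severity (mild, moderate, severe, healthy, above normal".
- **Weighted Cohen's kappa, formula.** Both i and j run from 1 to 4, in the numerator and in the denominator.
- **Aim and objectives, item 2.** Four levels: "ordinal (mild, moderate, severe anemia versus normal) measures longitudinally".

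**The concern.** These are the only two statistics the abstract names for agreement on the ordinal scale, and each is specified in two incompatible ways.

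For the C-index, the choice of denominator decides whether the device appears mediocre or excellent on identical data. The printed formula also has an unwelcome property. When SpHb puts two women with different CBC ranks into the same category, it has failed to separate them, yet that pair leaves the calculation. A device that compresses women into fewer categories is therefore not penalised for it.

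For weighted kappa, the number of categories is unsettled. An analyst could sum five, sum four and ignore the fifth, or merge the top two. These give different kappas and, on one reading, different sets of pairs.

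**Working it through.** **1. Category count.** Weighted kappa text: 5. C-index ranks: 5. Kappa formula: 4. Objectives: 4. The limit 4 is printed four times in the formula, so it is unlikely to be a PDF extraction fault. Only the stray leading fraction looks like one.

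**2. Ceiling of the C-index under the text.** With perfect agreement, concordant pairs are those in different categories, so the text version equals 1 minus the share of tied pairs. Take n = 900 (one site) and five equal categories of 180:

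- all pairs: 900 × 899 / 2 = 404,550
- tied pairs: 5 × (180 × 179 / 2) = 80,550
- text: (404,550 − 80,550) / 404,550 = 324,000 / 404,550 = 0.801
- formula: 324,000 / (324,000 + 0) = 1.000

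Equal categories are the most favourable case. An assumed split of 1/14/20/60/5% gives 234,009 / 404,550 = 0.578, and 2/25/25/46/2% gives 268,353 / 404,550 = 0.663. The formula gives 1.000 in both.

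**3. Imperfect agreement.** The article fixes neither a haemoglobin distribution nor cut-offs for the ordinal analysis, so these are assumptions: CBC Hb normal with mean 11 and SD 1.3 g/dL; cuts at 7, 10 and 11, with the 'above normal' cut at 13, 14 or 15; SD of the SpHb minus CBC difference 1.0; shift −0.8, 0 or +0.8 SD. The size 0.8 is the pilot figure in Sample size considerations. Its sign is not clearly stated there, so both are shown.

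Three versions are compared:

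- text: concordant / all pairs
- formula: concordant / (concordant + discordant)
- ties as one half: (concordant + 0.5 × pairs tied on SpHb only) / pairs with different CBC ranks

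Worked case, cut 13 and no shift, as shares of all pairs: concordant 0.484, discordant 0.046, CBC different but SpHb tied 0.148, CBC tied 0.322.

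- text: 0.484
- formula: 0.484 / (0.484 + 0.046) = 0.91
- ties as one half: (0.484 + 0.074) / (0.484 + 0.046 + 0.148) = 0.558 / 0.678 = 0.82

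| Upper cut | Shift (SD) | Text | Formula | Ties as one half | Ceiling under text |
|---|---|---|---|---|---|
| 13 | −0.8 | 0.46 | 0.92 | 0.81 | 0.68 |
| 13 | 0 | 0.48 | 0.91 | 0.82 | 0.68 |
| 13 | +0.8 | 0.47 | 0.92 | 0.81 | 0.68 |
| 14 | +0.8 | 0.39 | 0.93 | 0.79 | 0.63 |
| 15 | +0.8 | 0.36 | 0.92 | 0.76 | 0.63 |

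At cut 13, moving from no shift to +0.8 SD raises the formula from 0.913 to 0.921, while the half-tie version falls from 0.823 to 0.814. The share of CBC-different pairs that SpHb ties, which the formula discards, rises from 22% to 25%.

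**4. Weighted kappa, same assumptions, shift +0.8 SD.** 'Sum to 4' keeps expected counts from the five-category margins. 'Renormalised' recomputes them on the retained four-by-four table. 'Merged' puts 'above normal' into healthy.

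| Upper cut | Pairs outside 4×4 | Weights | Five categories | Sum to 4 | Renormalised | Merged (no pairs lost) |
|---|---|---|---|---|---|---|
| 13 | 24% | linear | 0.45 | 0.36 | 0.43 | 0.49 |
| 13 | 24% | quadratic | 0.62 | 0.48 | 0.53 | 0.59 |
| 14 | 9% | linear | 0.46 | 0.45 | 0.47 | 0.49 |
| 15 | 3% | linear | 0.48 | 0.48 | 0.49 | 0.49 |
| 15 | 3% | quadratic | 0.59 | 0.58 | 0.59 | 0.59 |

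At cut 13 the share outside the four-by-four table is 13% with no shift and 8% with −0.8 SD. At cut 15 with −0.8 SD it is below 1%.

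**The case against.** **Discordant might mean every pair that is not concordant.** The term is undefined, and on that reading text and formula agree. This is not the usual meaning, and it does not rescue the passage: ties would count as disagreement and a perfect device would be capped at about 0.80 or less.

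**The limit 4 may simply carry over from the four-level scale in the objectives.** This is plausible. If 'above normal' is merged into normal, no pair is lost. A reader might infer from the formula that up to a quarter of the data would be discarded and kappa biased well downward. The documents do not support that as fact. It requires the literal sum with five categories, a low 'above normal' cut-off and a positive shift, and the largest kappa gaps also require expected counts from five-category margins. With a cut at 15, or after renormalising with linear weights, the gap is close to zero. What stands is the inconsistent category count.

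**The choice of weights.** A reader might also object that linear and quadratic weights are both left open. That contradicts nothing in the article, and it is the kind of choice commonly settled in a separate analysis plan, so it is not part of this point.

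**These are secondary measures.** True. ICC and Bland–Altman carry Objective 1, the binary measures are separate, and no power or sample size figure changes.

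**Such detail belongs in a fuller plan.** This would answer an omission. Here the article prints explicit definitions and formulas that disagree with each other.

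**Conclusion.** The point holds as two contradictions in stated rules, both visible from the text alone.

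The C-index contradiction is the weightier. Its direction does not depend on assumptions: the text version is capped below 1 by ties, and the printed formula discards failures to separate women. Its size does depend on them. Under the assumptions above, C is about 0.36 to 0.48 by the text, 0.91 to 0.93 by the formula and 0.76 to 0.82 with SpHb ties as one half; the ceiling under the text is about 0.63 to 0.68, and never above about 0.80.

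The kappa contradiction is certain as a mismatch of four against five categories, but its numerical effect is not. Loss of pairs is conditional on the reading (about 0 to 24%), and kappa changes by about 0 to 0.15. The primary agreement analysis is untouched. This should be corrected before the ordinal results are computed.

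**What to change.** **C-index.** Define comparable pairs as pairs of participants whose CBC ranks differ, and use in both text and formula:

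C = (concordant + 0.5 × pairs tied on SpHb) / comparable.

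This reaches 1 under perfect agreement and 0.5 for a device that places everyone in one category. The bootstrap by participant can stay as written.

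**Weighted kappa.** Use one category set throughout. Either extend the sums to 1 to 5 and name five levels in the objectives, or merge 'above normal' into healthy, keep the sums at 1 to 4, and list four categories in both the weighted kappa and C-index sections.

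**Cost.** Edits to two formulas and a few sentences, with no new data and no change in sample size. The reported C will be lower than under the printed formula: about 0.76 to 0.82 instead of 0.91 to 0.93 in the illustrations above.

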**Methods and analysis:**

The proposed prospective cohort will be nested within the ongoing Pregnancy Risk and Infant Surveillance and Measurement Alliance (PRISMA) Maternal and Newborn Health (MNH) study. Three study sites (located in Zambia, Kenya, and Pakistan) will participate and collect hemoglobin data at five time points (<20 weeks, 20 weeks, 28 weeks, 36 weeks’ gestation, and six weeks postpartum). We will measure hemoglobin using a venous blood sample via hematology auto-analyzer complete blood count (gold standard) and the non-invasive device. The primary objective is to assess agreement between Masimo total hemoglobin and complete blood count and on a continuous scale using Intraclass Correlation Coefficient and Bland-Altman Analysis. The second objective is to assess agreement between the two measures on a binary scale using Positive Percentage Agreement and Negative Percentage Agreement, Cohen’s Kappa, and McNemar Test. On an ordinal scale, agreement will be measured using Weighted Cohen’s Kappa and Harrel’s Concordance Index. Lastly, we will assess factors that might affect the accuracy of Masimo total hemoglobin using linear mixed models.

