### Sample size considerations

**
*Total sample size*
**

The total sample size of 900 per study site will give 90% power for site-specific analyses to detect a systematic shift (defined as mean difference between each pair of SpHb and CBC divided by the standard deviation of all paired differences) of size 0.108 between the mean of SpHb measurements and the mean of CBC measurements. That is, if the SpHb system shifts from the reference CBC measurements by 10.8% of the SD of the mean difference, the probability that we will detect such a systematic shift using one sample t-test with significance level 0.05 is 90%. The total sample size of 900 will also give 80% power to detect a systematic shift of size 0.093*SD between the mean of SpHb measurements and the mean of CBC measurements. The SD can be calculated in the same way as those in the Bland Altman plots. However, 900 is a very conservative estimate of the sample size and would be sufficient to analyze the three sites independently. Based on our pilot data from Kenya and Pakistan, the mean difference between SpHb and CBC is approximately 0.8 times its SD; even a sample size as small as 19 pairs would provide 90% power using one-sample t-test.

In detecting the extreme differences (i.e. large absolute value) between the SpHb and CBC measures on the same sample, the sample size of 900 will give 99.99% probability to detect the top 1% largest values in the distribution of all differences. It will also give 98.90% probability to detect the top 0.5% largest values in the distribution of all differences, and 93.31%, 83.50%, 59.36% probability to detect the top 0.3%, 0.2%, 0.1% largest values in the distribution of all differences, respectively. With three repeated measures from each of the 900 participants, the listed probabilities are conservative estimates of chances in catching extreme values.

**
*Strata sample size*
**

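### Harrell's C-index is listed as a measure of agreement in anemia severity, but it measures rank association and, by its printed formula, cannot register a systematic shift of SpHb

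*Protocol article*

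**What the plan says.** The abstract (Methods and analysis) states: "On an ordinal scale, agreement will be measured using Weighted Cohen’s Kappa and Harrel’s Concordance Index". In Objective 2, the section on Harrell's concordance index falls under the heading for agreement of anemia severity. That section itself introduces the index as a goodness-of-fit measure.

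The section ranks five grades ("severe anemia=1, moderate anemia=2, mild anemia=3, healthy=4, above normal=5"). It defines concordance between two participants: "concordant pairs are the cases where the participant with higher rank" using SpHb is also the one with the higher rank using CBC.

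It gives two denominators. The text says "Comparable pairs are any pair of participants from the sample", that is, all n(n−1)/2 pairs. The printed formula divides the concordant pairs by concordant plus discordant pairs only, which leaves out every tied pair. No caveat says that the index ignores systematic over- or under-reading.

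Under Sample size considerations, the article reports from its pilot that "the mean difference between SpHb and CBC is approximately 0.8 times its SD". It gives neither the direction of that difference nor its SD in g/dL.

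**The concern.** A diagnosis of anemia depends on absolute cut-offs. A method agrees with the reference if it puts the same woman in the same grade. The C-index compares different women with each other and is satisfied when their order is kept. A device with a systematic shift can keep the order and still misgrade many women.

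The pilot suggests that a systematic difference is to be expected here. A C above 0.9, reported under an agreement heading beside a kappa near 0.45, would invite the reader to take the favourable figure as support for diagnostic validity.

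**Working it through.** **1. The plan's own figure.** The article states no value for C. Its nearest figure is the pilot bias of 0.8 SD, for which "even a sample size as small as 19 pairs would provide 90% power using one-sample t-test". The exact power of a two-sided one-sample t-test at alpha 0.05 with n = 19 and a difference of 0.8 SD is 0.909, so the statement reproduces. A shift of 0.8 SD is therefore the size to examine.

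**2. A small case.** Take three women with CBC grades 1, 2, 3 and SpHb grades 2, 3, 4. All 3 of 3 pairs are concordant and none is discordant, so C = 3/(3 + 0) = 1. Exact agreement is 0 of 3. No pair is tied, so this result does not depend on the choice of denominator.

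**3. The general result for the printed formula.** If SpHb is a non-decreasing function of CBC (for example CBC plus a constant), both grades rise together with true hemoglobin. No pair can then be discordant, and C = conc/(conc + 0) = 1 whatever the hemoglobin distribution or cut-offs, as long as one concordant pair exists.

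**4. Size under assumed values.** Assumptions not in the article: CBC normal with mean 11 and SD 1.3 g/dL, grade cuts 7/10/11/14 g/dL, normal noise with SD 1 g/dL in the noisy cases, and both directions of bias. Three definitions were computed:
- printed: conc/(conc + disc);
- text: conc/all pairs;
- conventional Harrell: pairs untied on CBC, with SpHb ties counted as one half.

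| Scenario | C, printed | C, text | C, conventional | Linear weighted kappa |
|---|---|---|---|---|
| Perfect agreement | 1.000 | 0.634 | 1.000 | 1.00 |
| Noise, no bias | 0.913 | 0.440 | 0.814 | 0.55 |
| Noise, +0.8 SD | 0.927 | 0.392 | 0.785 | 0.46 |
| Noise, −0.8 SD | 0.918 | 0.429 | 0.808 | 0.45 |
| Constant +1 g/dL | 1.000 | 0.388 | 0.806 | 0.41 |
| Constant +2 g/dL | 1.000 | 0.296 | 0.734 | 0.10 |

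The noise-only row shows how the definitions relate. Concordant pairs are 0.440 of all pairs and discordant pairs 0.042, so the printed C is 0.440/(0.440 + 0.042) = 0.913. The remaining 0.518 are tied on at least one method.

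Exact grade agreement is 51% at +1 g/dL and 30% at +2 g/dL.

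**5. Range of assumptions.** The grid had CBC mean 10.5 to 11.5, CBC SD 1.2 to 1.5, SD of differences 0.7 to 1.3 g/dL, an above-normal cut of 13 or 15, and bias +0.8 or −0.8 SD, which makes 72 biased scenarios. The printed C did not fall in any of them. It rose by about 0.001 to 0.025, while linear weighted kappa fell by about 0.06 to 0.12.

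**6. An over-read that varies between women.** With the over-read uniform from 0 to +2 g/dL (CBC mean 11, SD 1.3, as above), the printed C is about 0.98 and not 1, while linear weighted kappa is about 0.45 to 0.47 depending on the above-normal cut.

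**The case against.** The strongest reply is that the shift will be seen elsewhere. Weighted kappa is planned on the same grades, Bland-Altman estimates the mean difference directly, McNemar tests directional disagreement, and Objective 3 models SpHb minus CBC. No decision rule, success threshold or sample size rests on C. All of this stands and limits the harm. It does not turn a ranking index into a measure of agreement.

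The second reply is that the numbers depend on how ties are handled. This also stands. Under the text denominator or the conventional Harrell definition, a +0.8 SD bias lowers C (0.440 to 0.392, and 0.814 to 0.785), and a constant over-read does not score 1 in the example. Neither version rescues the index. By the text denominator, perfect agreement scores only about 0.63. The conventional version moves mainly because bias creates ties, and it falls by about 0.03 or less in the example when kappa falls by about 0.10.

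The third reply is that the cross-tabulation is detail for the full plan, since weighted kappa already uses the observed-count matrix. That is fair for the table alone. The label, role and formula of the C-index, however, are fixed in the article.

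**Conclusion.** The point holds as one of labelling and interpretation. The C-index as defined measures rank association, and this follows from the text without any assumption. By the printed formula a constant or order-preserving shift scores exactly 1, and a bias of 0.8 SD did not lower C in any scenario tried, while kappa dropped by about 0.1. The numerical sizes rest on the assumed hemoglobin distribution, cuts and noise, none of which the article gives in full.

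A reader might infer more than the document supports:
- That any device that over-reads every woman scores 1. This needs an order-preserving over-read and the printed denominator; a varying over-read gave about 0.98.
- That the pilot bias improves C. The rise is at most about 0.025, is specific to the printed formula, and for over-reading reverses in the example under the other two definitions.
- That the pilot shows anemic women being moved to milder grades. The pilot's direction and its SD in g/dL are not stated.

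**What to change.** In the abstract and in Objective 2, stop calling the C-index a measure of agreement. Either drop it, or label it rank association (discrimination), state that it does not reflect systematic over- or under-reading, and do not use it to support diagnostic validity.

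Base ordinal agreement on weighted kappa together with, for each CBC grade, the share of women whom SpHb places in the same, a milder or a more severe grade. Use the participant-level bootstrap intervals already planned.

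If C is kept, reconcile the text denominator with the printed formula and state how pairs tied on SpHb, on CBC or on both are counted.

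The cost is wording and one cross-tabulation of data already planned, plus the loss of a figure that may look more favourable than the agreement measures.

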### Objective 3: Factors affecting differences between SpHb and CBC

In order to assess factors that might affect the accuracy of SpHb, we will include the following characteristics in linear mixed models in order to assess differences between paired SpHb and CBC measurements. These variables will be collected during the enrollment visit, ANC visit, and or during the postpartum visit.

Maternal age,Anemia severity stratum,Nutritional status (e.g., iron deficiency),HIV status (Zambia and Kenya sites only),Malaria status (Kenya site only),Helminth infection status (Kenya site only),Gestational age at assessment and at first ANC visit,Technician,Time between SpHb collection and CBC collection,Participant’s early pregnancy BMI (measured at first ANC visit),Mid upper arm circumference (MUAC),Study site,Tobacco use,Estimated plasma volume (PV)
^
17
^ where Kaplan-Hakim formula
^
18
^ estimates PV as: 

PV(cPV)=(1−hematocrit)∗[a+(b∗weightinkg)]

Where,
*a = 1,530* in males and
*864* in females, and

*b = 41* in males and
*47.9* in females.

We will assess differences between these subgroups as follows:

*Candidate forms of the differences in hemoglobin levels (outcome):*

Differences (
*Δ* =
*SpHb*–
*CBC*),Absolute differences |
*Δ*|,Log(SpHb) - log(CBC) = log(SpHb/CBC).

*Comparison of the outcomes across different categories:*

Contingency tables will be constructed where the distribution of the outcome (differences) will be compared across different levels of the risk factors. For example, mean/SD/IQR of the outcome will be listed side by side for each site and p-values using mixed models comparing the distributions between different locations will be reported.

*Plot of the outcome versus risk factors:*

Lowess or kernel smoothing curves will be fitted for the relationship between the outcome and continuous risk factors such as true Hb values.

*Univariate analysis of candidate risk factors:*

One linear mixed model will be fitted for each candidate risk factor. Candidate risk factors will be tested one at a time and marginal associations between the size of measurement errors and each risk factor will be reported as change per sample SD or change w.r.t. reference level, 95% confidence interval and p-values. All effect sizes and CI can be reported in a forest plot

*Multivariate analysis of selected candidate risk factors:*

Elastic net penalized regressions (R package glmnet) with cross validation selected tuning parameters will be employed to select a set of harmonious and prognostic covariates. One multivariate linear mixed model will be fitted with control of the collinearity (VIF <8) and manual tuning using clinical knowledge. The predictive accuracy of the final model will be assessed using R
^2^ and residual plots.

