### Study sample

**
*Recruitment of participants*
**

A sample of 900 pregnant women from each site will be selected from the PRISMA study primary cohort, for a total of 2700 participants. Participants may be recruited sequentially through household-based or facility-based pregnancy surveillance (e.g., the first 900 women enrolled in PRISMA will also be included in this study from the date of protocol approval per site).

**
*Eligibility criteria*
**

Any participant that is eligible for the PRISMA study is also considered eligible for this study. However, research staff may exclude women from the study, based on the presence of injury, deformity, tattoo, or birthmark that interferes with Masimo sensor placement or performance or a finger size that does not appropriately fit the device. Presence of henna, nail polish or long nails is not an exclusion criterion, but staff will record information about these factors as they might interfere with the Masimo device performance.

**
*Consent*
**

PRISMA MNH uses a multiphase process to recruit women through pregnancy surveillance. Consent or assent will be obtained from pregnant women after a pre-screening process to determine eligibility in the PRISMA MNH study.

**
*Study status*
**

The parent PRISMA MNH study began recruiting and enrolling pregnant women on 22 September 2022 (Pakistan), 23 November 2022 (Kenya), and 15 December 2022 (Zambia). The study is planned to complete enrollment at the end of 2025. 

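### Objective 3 tests each continuous factor as one slope, and the planned smoothing curves are not linked to the tested model, so an effect at both extremes can be missed or misdescribed

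*Protocol article*

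**What the plan says.** The relevant text is in the Protocol article, section Objective 3: Factors affecting differences between SpHb and CBC.

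- **Model.** "One linear mixed model will be fitted for each candidate risk factor".
- **Effect measure.** "each risk factor will be reported as change per sample SD or change w.r.t. reference level, 95% confidence interval and p-values". These estimates may be shown in a forest plot.
- **Outcome forms.** The candidates are the signed difference, the absolute difference and the log ratio.
- **Descriptive look at shape.** "Lowess or kernel smoothing curves will be fitted for the relationship between the outcome and continuous risk factors such as true Hb values". In tables, "the distribution of the outcome (differences) will be compared across different levels of the risk factors"; study site is the worked example, and no cut-points are given for BMI, MUAC or age.
- **Multivariable step.** An elastic net selects covariates. Then "One multivariate linear mixed model will be fitted with control of the collinearity (VIF <8) and manual tuning using clinical knowledge", with R-squared and residual plots as checks on the final model.

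No spline, quadratic or categorised term is named for any continuous factor at either step. No sentence says that the smoothed curves decide the form of the tested model.

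**The concern.** For a categorical factor, change against a reference level can take any shape. For a continuous factor, change per SD is one straight line. Objective 3 asks what affects the size of the measurement error, and the absolute difference is one of its outcomes. Error size can plausibly grow at both ends of a factor. A straight line averages the two ends and can cancel them.

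The slope, its interval, its p-value and the forest plot are the formal answer to Objective 3, and the elastic net is described without non-linear terms. A factor with a U-shaped effect could appear unrelated in those outputs and be removed before the final model, where the residual plots come too late to bring it back. The descriptive curve might show the bend, but no rule says what then follows.

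**Working it through.** **The plan's own figures.** None is given for Objective 3. The nearest is the shift test under Sample size considerations: 900 pairs and a shift of 0.108 SD. The noncentrality is 0.108 × √900 = 3.24, and two-sided power at 0.05 is 89.9% (stated: 90%). It reproduces, but it says nothing about functional form.

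**Inputs.** From the protocol: 900 women per site, 2700 in all, five visits, one slope per continuous factor. Assumed, because the protocol gives no figures: between-woman SD of the difference 0.6 g/dL and visit SD 0.8 g/dL (total SD 1); a woman-level factor x standardised to mean 0 and SD 1; true effect c·x², with c = 0.05 or 0.1. At x = ±2, c = 0.1 means 0.4 g/dL.

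**Step 1: what the slope estimates.** With Var(x) = 1, slope = Cov(x, c·x²) = c·E[x³], that is, c times the skewness of x.

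- Symmetric x: skewness 0, so the slope is 0 at any sample size.
- Lognormal x with log-SD 0.2: skewness = (e^0.04 + 2)·√(e^0.04 − 1) = 3.041 × 0.202 = 0.614. The slope is 0.03 at c = 0.05 and 0.06 at c = 0.1.

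**Step 2: rejection rates.** The SD of a woman's mean difference is √(0.36 + 0.64/5) = 0.699. Simulation with 2000 replicates, slope test against a 3-df restricted cubic spline test (4 knots):

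| Factor | c | n | Slope per SD | Slope test rejects | Spline test rejects |
|---|---|---|---|---|---|
| either | 0 | 900 or 2700 | 0.00 | about 5% | about 5% |
| symmetric | 0.05 | 900 | 0.00 | 5% | 70% |
| symmetric | 0.05 | 2700 | 0.00 | 6% | over 99% |
| symmetric | 0.1 | 900 | 0.00 | 7% | 99.9% |
| symmetric | 0.1 | 2700 | 0.00 | 6% | 100% |
| right-skewed | 0.05 | 900 | 0.03 | 26% | about 80% |
| right-skewed | 0.1 | 900 | 0.06 | 70% | over 99% |
| right-skewed | 0.1 | 2700 | 0.06 | over 98% | 100% |

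At 900 women, the 2-df test of non-linearity alone rejects in about 76% to 77% of trials at c = 0.05 and over 99% at c = 0.1, for either factor.

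**Step 3: what a detected slope conveys.** In the skewed case with c = 0.1, a slope of 0.06 reads as a steady rise of 0.06 × 4 = 0.24 g/dL from −2 to +2 SD. The truth is no difference between those two points, with both 0.4 g/dL above the centre.

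**Step 4: the absolute difference.** Take a mean difference of 0.8 SD (the protocol's pilot value) and error SD growing as 1 + k·x², with k = 0.05 to 0.2, x symmetric, 900 women and one observation per woman. The slope test on the absolute difference rejects in 7% to 14% of trials, and a joint linear-plus-quadratic test in 33% to over 99%.

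**Step 5: does the absolute value itself create a V?** With mean difference 0.8 SD and slope b per SD of the factor, the signed difference crosses zero at x = −0.8/b: −8 for b = 0.1, −4 for b = 0.2, −2 for b = 0.4. For a normal difference, the expected absolute difference rises monotonically over ±2 SD for b from 0.1 to 0.4. At the pilot shift there is no V from this source.

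**The case against.** **Only an article is shown, and covariate form is usual analysis-plan content.** This stands for details such as knots. But the article itself fixes the effect measure and the test for each factor, so how that choice performs can be judged.

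**Shape is already examined.** The smoothing curves, the tables by level, the manual tuning and the residual plots could all reveal a bend. This largely stands. A reader might infer that Objective 3 as a whole would report no effect. The documents do not support that: the risk lies in the slope, interval, p-value, forest plot and covariate selection, not in the descriptive output.

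**The protocol does not say which factors stay continuous.** Correct. BMI, MUAC or age entered as categories would escape the problem. The point applies only to factors kept continuous.

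**Body size and finger fit.** A reader might infer that the protocol points to a U-shaped effect of body size. It does not. The Eligibility criteria let staff exclude women for "a finger size that does not appropriately fit the device", so the extremes may be absent from the data. Finger size is not a listed factor, and that BMI or MUAC tracks finger fit is an assumption. Plasma volume, computed from weight, also carries body size. The example is illustrative only.

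**Skewed factors are still detected.** True in large part, as the table shows. What remains is a misleading slope rather than a missed factor.

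**A spline costs power if the effect is linear.** Also true. For a linear 0.06 g/dL per SD at 900 women the noncentrality is 900 × 0.06²/0.488 = 6.64, which gives power of about 0.73 on 1 df and 0.56 on 3 df. This argues against replacing the slope, not against adding to it.

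**Conclusion.** The point holds in a limited form. For a factor kept continuous, the formal Objective 3 result is one slope, and the planned curves have no stated route into the tested model, the forest plot or the elastic net. If the factor is symmetric and the effect U-shaped, the slope test stays near its nominal 5% at either sample size (5% to 7% here), while a flexible test at c = 0.1 almost always finds the effect. If the factor is right-skewed, the slope is often significant but describes the wrong shape.

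These sizes rest wholly on assumed curvature, variances and factor distributions, and on a factor that is constant within a woman; the interval between SpHb and the blood draw varies by visit and was not modelled. Nothing in the documents shows that any listed factor has such an effect, and removal by the elastic net is a risk, not a certainty. This is a worthwhile refinement of a secondary, descriptive objective. It does not touch Objectives 1 and 2.

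**What to change.** Keep the per-SD slope as planned. For each factor kept continuous:

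1. Fit the same mixed model with a restricted cubic spline, for example 4 knots at fixed percentiles, and report the test of non-linearity beside the slope.
2. Where non-linearity is evident, report fitted differences with 95% CI at set percentiles (for example the 5th, 50th and 95th) next to the slope in the table and forest plot.
3. Offer the non-linear terms for that factor to the multivariable selection as one group.
4. State in one sentence that the smoothing curves illustrate these fits and do not by themselves decide the model.

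Cost: a longer results table, two extra degrees of freedom per continuous factor in the spline model, and a few more tests. If seven factors were kept continuous (age, two gestational ages, time interval, BMI, MUAC, plasma volume), about 7 × 0.05 = 0.35 would be flagged by chance per outcome form, so the tests should be read as descriptive. Because the slope test stays, its power for a linear effect is unchanged. No new data are needed.
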